### Patient Characteristics and Baseline Comparison

Discrete baseline variables will be summarized by frequencies and percentages. Percentages will be calculated using the number of patients for whom data is available. Continuous variables will be summarized by using mean and SD, and median and interquartile range (Q1-Q3). No adjustment for clustering will be applied when comparing baseline characteristics. Standardized differences between groups in baseline characteristics will be reported. A less than 0.1 standard difference will be used to indicate a negligible difference in the mean or proportion of a baseline variable between treatment groups [14].

Variables for baseline measures will be tabulated, including demographic (age, sex, ethnicity), socioeconomic status (education level, household income, health insurance), anthropometric measurements (weight, BMI, waist circumference, BP), smoking status, diabetic complications, laboratory data (HbA_1c_, FBG, LDL-C, serum creatinine), and score of the summary of diabetes self-care activities.

Cluster characteristics will be summarized in stratified and overall randomization groups. The cluster characteristics at baseline are age of the community or village doctors, smartphone operation system (iOS or Android) that the community or village doctors were using, and number of patients with T2D registered.

### Compliance to Basic Intervention Service

Data on the receipt of intervention provided for standardized diabetes management services have been routinely collected by the app Graded ROADMAP, including the frequencies and the results of FBG or postprandial blood glucose tests, BP measurements, and patient referrals from primary care clinics to the upstream hospitals at the county or district level. According to the protocol, each patient is due to receive at least two blood glucose tests (FBG, postprandial blood glucose, or both) and one BP measurement per month. Although necessary referral is encouraged when indicators are present, there is no requirement for the referral rate.

Among the intervention group, the mean times of health services received per patient per month; the percentage of patients achieving the protocol-required measurement frequency; and the mean values of FBG, postprandial blood glucose, and BP will be illustrated in separate figures with a double y-axis.

### Exposure to Intensive Intervention

Within the intervention group, the frequency of patient’s log-ins to the Your Doctor app will be described in numbers and percentages of frequency from 0 to >12 over the 1-year study period, and as a categorical variable in frequency ≥4 or <4. A patient with the frequency ≥4 times per year (referring to the essential public health service recommendation) will be defined as a complier to intensive intervention and, thus, form the intensive intervention subset for further comparison between basic and intensive intervention.

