### Intervention

Besides a standard training workshop for the contracted service providers (community, township, and county level doctors) in the intervention arm, the key components of intervention were one BP measurement and two blood glucose monitoring tests (at least one fasting blood glucose [FBG]) monthly, instruction for lifestyle change and medication accordingly, timely referral if an indicator is present, and quarterly performance review for the contracted service team. A mobile health–based information system, Graded ROADMAP, was developed and employed to support the contracted doctor team delivering the intervention. Another smartphone app, Your Doctor, was available for participants in the intervention arm to facilitate health education and communication between the designated doctors and patients. The use of Your Doctor depended on participants’ willingness and capability of using the smartphone app. At the end of this study, all the participants in the intervention arm were divided into two subgroups based on the actual use of Your Doctor: a basic intervention subgroup in which participants have logged in less than 4 times to the app throughout the 1-year follow-up and an intensive intervention subgroup in which the participants have at least 4 log-ins within 1 year.

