### Sample Size

A sample size of 16,416 participants (19 patients per community) at 1 year provided an 89% power (2-sided α=.05) to detect a ≥5% absolute increase in the primary outcome for the intervention group. The sample size calculation assumes that 40% of participants will have well-controlled HbA_1c_ levels (<7%) at the end of the study in the control group [6], with an intraclass correlation coefficient of 0.15 based on our previous Observational Registry of Basal Insulin Treatment (ORBIT) study [13]. Furthermore, assuming that 50% of participants (ie, 576 clusters with a smaller average cluster size of 9-10 participants) in the intervention group will receive the intensive intervention (at the patients’ discretion), it will need 93% to detect absolute increases of 5% HbA_1c_ control, when compared to the basic intervention group (576 clusters with an average cluster size of 9-10 patients). Accounting for a potential loss to follow-up of 14% of patients, the study aimed to recruit 19,008 patients with T2D from 864 communities or villages (576 in intervention and 288 in control, with a 2:1 ratio) in 24 provinces in mainland China, which equates to an average of 22 patients from each community or village.

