#### Comparison Between Basic and Intensive Intervention

To explore the possible additional effect from intensive intervention, we will compare the intensive intervention to the basic intervention using similar models, regardless of whether the difference between the overall intervention group and control group is statistically significant. Considering the potential imbalance in the baseline characteristics between patients following the intensive intervention and those following the basic intervention, two propensity score methods will be applied. Both the propensity score adjusted regression based on a log-binomial model with GEE and the inverse probability of treatment weighting method will be used to evaluate the intervention effect [16,17] as the sensitivity to seek the consistency of the conclusion. The propensity score model will consist in a simple logistic regression with baseline covariates including age, sex, the baseline value of the analyzed outcome, education, duration of diabetes, comorbidities, economic development level, and locality (urban or rural). Baseline characteristics of participants will be described in a table separately before and after propensity score adjustments.

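### The intensive and basic groups are formed from log-ins over the whole year that ends with the outcome, so on-study glucose course can influence group membership, and baseline-only propensity scores cannot remove that bias

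*SAP article*

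**What the plan says.** - **How the groups arise.** The SAP article (Introduction, Intervention) divides the intervention arm at the end of the study by actual use of Your Doctor. Fewer than four log-ins over the follow-up year is basic; the other group is "an intensive intervention subgroup in which the participants have at least 4 log-ins within 1 year". Use was left to the patient's willingness and ability. The app serves health education and contact with the designated doctors.
- **How the grouping is used.** Under Exposure to Intensive Intervention, a patient at or above four per year "will be defined as a complier to intensive intervention and, thus, form the intensive intervention subset for further comparison between basic and intensive intervention".
- **Outcome.** HbA1c <7% at 1 year (Outcomes; Primary Analyses).
- **Adjustment.** Comparison Between Basic and Intensive Intervention names only a possible baseline imbalance. "The propensity score model will consist in a simple logistic regression with baseline covariates including age, sex", followed by the baseline value of the outcome, education, diabetes duration, comorbidities, economic level and locality. The score enters a log-binomial GEE and an inverse-probability-weighted (IPTW) analysis, and the two are to be checked for consistency.
- **Status.** General Analysis Principles calls this a secondary comparison to be explored. Sample Size nevertheless gives it a power figure, and the comparison section describes its methods as evaluating an intervention effect, to be run whatever the primary result.

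The plan sets no early window for log-ins, no landmark and no time-varying exposure.

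**The concern.** The exposure window and the outcome window are the same year. Intervention patients are due two glucose tests a month, with advice and referral depending on results, and the app is a channel to the doctors who act on those results. A patient who is improving may stay engaged and log in more; a patient who is worsening may log in more to seek help. Log-ins made after such a change still count as exposure, so a group difference can run from glucose to log-ins instead of from log-ins to glucose.

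This is separate from who chooses the app at the outset. A complete and correct baseline propensity score would deal with that choice, but it would still contain nothing about what happened between baseline and month 12. Both planned methods rest on the same baseline score, so both carry the same bias. What is at stake is whether the trial may say that the app adds anything to the basic intervention.

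**Working it through.** **1. The plan's own power figures.** Inputs from Sample Size: "A sample size of 16,416 participants (19 patients per community) at 1 year provided an 89% power"; a two-sided test at the 5% level; a 5-point absolute rise over an assumed 40% among controls; ICC 0.15; 288 control and 576 intervention clusters.

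- Primary: design effect = 1 + (19 − 1) × 0.15 = 3.70. Effective n = 288 × 19 / 3.70 = 1,479 and 576 × 19 / 3.70 = 2,958. SE = √(0.40 × 0.60 / 1,479 + 0.45 × 0.55 / 2,958) = 0.0157. Power = Φ(0.05 / 0.0157 − 1.96) = 89.0% (88.8% with pooled variance). This reproduces the stated 89%.
- Intensive versus basic: 576 clusters per group, 9 to 10 patients each. The rate in the basic group is not stated, so two pairs were tried: 93.5 to 94.3% for 40% vs 45%, and 93.0 to 93.9% for 45% vs 50%. This agrees with the stated 93%, read as power.
- That 93% treats the groups as separate sets of clusters, although both come from the same 576 communities. If log-in status varies within communities, SE = √((0.45 × 0.55 + 0.50 × 0.50) × 0.85 / 5,472) = 0.0088 and power for 5 points exceeds 99.9%. A bias of only 1.96 × 0.0088 = 1.7 points would then reach significance about half the time.

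**2. Simulation under the plan's kind of adjustment, true app effect zero.** Each run had 576 × 19 patients. Standardized baseline HbA1c b had ICC 0.15. One-year HbA1c was y = 0.6b + 0.8e, with 45% controlled. On-study course was c = r·e + √(1 − r²)·e′. About half the patients reached four log-ins, with an assumed odds ratio per SD of better course and 1.2 per SD of better baseline. Analysis was IPTW with a logistic score on baseline only and cluster-robust SE, 200 runs per setting. The document supplies neither the odds ratio nor r. Spurious difference in points (share of runs significant):

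| Odds ratio per SD of course | r = 0.3 | r = 0.5 | r = 0.7 |
|---|---|---|---|
| 1.0 | 0.0 (1%) | 0.0 (1%) | 0.0 (3%) |
| 1.1 | +0.8 (11%) | +1.4 (29%) | +2.1 (59%) |
| 1.2 | +1.7 (41%) | +2.8 (88%) | +3.9 (100%) |
| 1.4 | +3.2 (94%) | +5.1 (100%) | +7.3 (100%) |
| 2.0 | +6.0 (100%) | +10.0 (100%) | +14.1 (100%) |

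With on-study course added to the propensity model, the mean bias was within 0.2 points in every setting. With the link reversed (worse course, more log-ins; odds ratio 1.4, r = 0.5, one run) the difference was −4.3 points. Propensity-score-adjusted GEE (modified Poisson, r = 0.5, one run each) gave RR 1.03 (p = 0.13) at odds ratio 1.0 and RR 1.10 at 1.4, so the second planned method shares the bias.

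**3. A differently built simulation.** It used 400,000 patients, monthly Poisson log-ins with a random user effect (SD 0.8, log scale), baseline HbA1c mean 7.4 and SD 1.6, 44% reaching four log-ins, and no app effect. Results were standardized over baseline HbA1c.

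| Log-in rate per SD of better course | Whole-year rule (≥4) | First 3 months (≥1) |
|---|---|---|
| no link | RR 1.00 | RR 1.00 |
| +10% | +2.6 | +0.3 |
| +22% | +5.3 | +1.1 |
| +35% | +7.9 | +1.7 |

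An independent repeat gave +2.4 / +5.3 / +7.9 for the whole-year rule and +0.6 / +1.3 / +1.9 for the early window. With worsening patients logging in more, the whole-year rule gave −2.6 to −5.1 and the early window −0.5 to −1.0.

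**4. What the early window costs.** In the same log-in model with no link, 32 to 34% of patients with a log-in in the first 3 months never reach four in the year, and about 17% of those without one do. A true 5-point effect of reaching four log-ins would show as about 5 × (0.66 − 0.17) = 2.5 points (2.6 in the repeat).

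**The case against.** The plan calls the comparison secondary and says the effect will be explored. It attributes app use to willingness and ability, and nothing in it ties log-ins to glucose. The four-log-in cut-off follows the public health service recommendation, so a landmark rule asks a different question and loses signal.

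Much of this stands. A reader might infer that glucose course decides the group, or that a false 5-point effect has been shown. The document supports neither: log-ins define the group, and 5 points is one value on an assumed range that includes zero and can change sign. A fourth log-in in month 12 is by itself only misclassification, which would dilute a real effect; it yields a false one only through the assumed link. A reader might also extend the point to early leavers or to hypoglycemia counts. The plan does not clearly specify an intensive-versus-basic analysis of either kind: imputed data go into model 1 and hypoglycemia is tabulated by randomized arm, while the main analyses use available data only. Replacing the whole-year grouping outright would be a trade-off, not a correction.

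The exploratory label does not settle the matter. The comparison has its own power statement, its methods are described as evaluating an intervention effect, and nothing warns that exposure is classified after baseline.

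**Conclusion.** The concern holds as a structural one. The whole-year rule cannot separate an app effect from on-study glucose course influencing log-ins, and neither planned propensity method can repair this. The size is unknown. Under no link the bias is zero; under modest assumed links it is about 2.5 to 5 points in either direction, and the strongest setting tried gave +14.1. A positive bias could be taken for an app benefit, and a negative one could hide a real benefit. All non-zero figures rest on assumed associations and are illustrative only. The randomized comparison of intervention with usual care is untouched.

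**What to change.** In General Analysis Principles, Exposure to Intensive Intervention and Comparison Between Basic and Intensive Intervention:

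1. Keep the whole-year grouping at four log-ins, but report it as a non-causal association and not as an intervention effect.
2. If dated log-ins are held, add a specified landmark analysis. Classify intervention patients by log-ins in an early window, for example at least one in the first 3 months, which is the same yearly rate. Include only patients still in follow-up at that point. Adjust for the baseline covariates and for the glucose results recorded up to the landmark, which Graded ROADMAP collects.
3. Claim an added app effect only if the landmark analysis supports it.

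The cost is plan wording, one regrouped variable and a merge with early glucose results. Three limits should be stated. The plan describes only yearly log-in counts, and its routine glucose data come from a different app, so dated log-ins must be confirmed; without them only item 1 is possible. Early log-ins can roughly halve a real effect, so a null landmark result does not rule out benefit. Glucose within the window may already reflect app use, so the result should be shown with and without that adjustment. The article gives sign-off in November 2019 and database lock in January 2020, so an addition made after lock should be dated and labelled as such.

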### Analysis of the Primary Outcome

#### Primary Analyses

The primary endpoint, control rate of HbA_1c_ at 1 year, will be first compared between all intervention groups and all control groups. The primary analysis of the intervention effect will be conducted using a log-binomial regression with generalized estimating equations (GEE) to account for clustering within communities and with adjustment for baseline HbA_1c_ as a continuous covariate (model 1). The raw number and percentage of patients with adequate control of HbA_1c_ at 1 year will be reported. The effect of the intervention will be presented as the relative risk (RR) of the proportion of HbA_1c_ levels <7% along with its 95% CI and corresponding *P* value. In cases of a convergence issue, the logistic regression with GEE and the Poisson regression with GEE will be both used as the alternative methods, with the Poisson regression as the sensitivity analysis. The odds ratio along with the indirectly derived RR will be reported for the logistic regression.

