**Secondary outcomes**						
	FBG^d^ < 7.0 mmol/L		xxx (xx.x)	xxx (xx.x)	x.xx (x.xx-x.xx)	.xx
	BP^e^ < 140/80 mmHg^f^		xxx (xx.x)	xxx (xx.x)	x.xx (x.xx-x.xx)	.xx
	LDL-C^g^ < 2.6 mmol/L		xxx (xx.x)	xxx (xx.x)	x.xx (x.xx-x.xx)	.xx
	Composite diabetes control^h,i^		xxx (xx.x)	xxx (xx.x)	x.xx (x.xx-x.xx)	.xx

^a^Primary model: log-binomial regression with generalized estimating equation (GEE) with adjustment of the baseline value of the analyzed outcome and clustering. The logistic regression with GEE will be employed as the alternative method in case of non-convergence, with indirectly derived relative risk reported.

^b^RR: relative risk.

^c^HbA_1c_: glycated hemoglobin.

^d^FBG: fasting blood glucose.

^e^BP: blood pressure.

^f^Only systolic blood pressure at baseline and clustering were adjusted in the primary model for BP control.

^g^LDL-C: low-density lipoprotein cholesterol.

^h^Composite diabetes control: defined as HbA_1c_ level <7.0%, BP <140/80 mmHg and LDL-C <2.6 mmol/L.

^i^No baseline variable was adjusted in the primary model for the composite diabetes control.

**Table 3 table3:** Estimated effects of intervention compared to control on the change from baseline of continuous outcomes.

Secondary continuous outcome		Control, mean (SD)	Intervention, mean (SD)	Primary model^a^	
				Mean differences (95% CI)	*P* value

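### If the log-binomial model fails, the tabulated primary RR comes from a logistic model by an unstated route, while the model that estimates the RR directly is only a sensitivity analysis

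*SAP article*

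**What the plan says.** SAP article, Primary Analyses: the main model is a log-binomial GEE clustered on community, "and with adjustment for baseline HbA_1c_ as a continuous covariate (model 1"), and the effect is reported as an RR with 95% CI. No transformation or non-linear form of the covariate is mentioned. If convergence fails (no criterion is given), logistic GEE and Poisson GEE are both fitted, "with the Poisson regression as the sensitivity analysis. The odds ratio along with the indirectly derived RR will be reported for the logistic regression".

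Table 2, footnote a, names only the logistic fallback: "The logistic regression with GEE will be employed as the alternative method in case of non-convergence, with indirectly derived relative risk reported". Neither place says how the RR or its CI follows from the logistic fit.

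Imputed Data Analyses pools the model 1 coefficient across ten imputed data sets into one RR. Analysis for Binary Categorical Outcomes reuses model 1 for FBG, BP and LDL-C. Table 2, footnote f, limits the BP model's baseline adjustment to systolic pressure, and footnote i states that the composite has no baseline covariate.

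**The concern.** A log link requires every fitted probability to stay at or below 1. The covariate is the same measurement that, one year later, is cut at 7% to form the outcome, so it may be strongly prognostic. Patients with low baseline values can then push the fitted probability to its limit and the fit may fail. The fallback is therefore a realistic branch of the primary analysis.

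In that branch the ranking matters. An OR adjusted for a prognostic covariate is a conditional OR and is further from 1 than the marginal OR for the same pair of risks. Converting it with the overall control risk carries that gap into the RR. Poisson GEE needs no conversion. Because the article names no route from OR to RR, two analysts following it could publish noticeably different primary RRs.

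**Working it through.** **Inputs from the documents (Sample Size).** "A sample size of 16,416 participants (19 patients per community) at 1 year"; "The sample size calculation assumes that 40% of participants will have well-controlled" HbA1c in the control arm; "with an intraclass correlation coefficient of 0.15 based on our previous Observational Registry of Basal Insulin Treatment (ORBIT) study"; 576 intervention and 288 control clusters; and the design "provided an 89% power (2-sided α=.05) to detect a ≥5% absolute increase in the primary outcome for the intervention group".

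**The plan's own figure first.** Design effect = 1 + (19 - 1) × 0.15 = 3.70. Effective control n = 288 × 19 / 3.70 = 1,478.9; intervention is twice that, 2,957.8. SE = √(0.40×0.60/1,478.9 + 0.45×0.55/2,957.8) = 0.01568. Power = Φ(0.05/0.01568 - 1.96) = Φ(1.23) = 89.0% (88.8% with pooled variance). The stated 89% reproduces.

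**True effect at the design values.** RR = 0.45/0.40 = 1.125. Marginal OR = (0.45/0.55)/(0.40/0.60) = 1.227.

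**Assumptions, not in the documents.** Baseline HbA1c mean 7.5% or 8.0%, SD 1.5% or 1.8%, normal or right-skewed; logit slope for control at 1 year from 0 to -1.2 per 1% HbA1c.

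**Step 1: does the log-binomial GEE converge?** One trial of 864 clusters of 19 was simulated in each of 12 scenarios (slopes -0.5, -0.8, -1.2). The model converged in 3, all at -0.5, and failed in 9, including all eight at -0.8 or -1.2. A second set (mean 7.6, SD 1.6, 12 runs per setting) gave a usable fit in 12/12 runs at -0.3 and -0.5. At -0.8 it was usable in 1/12 (normal) and 5/12 (skewed), and at -1.2 in 1/12 and 0/12. The fits were made outside SAS, so the counts are indicative.

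**Step 2: size of the simple conversion.** For each assumed slope, find the conditional OR that yields 40% versus 45%, then apply RR = OR/(1 - p0 + p0 × OR) with p0 = 0.40. Example (normal, mean 7.5, SD 1.5, slope -0.8): OR = 1.300, so RR = 1.300/(0.60 + 0.40 × 1.300) = 1.300/1.120 = 1.161. The excess is inflated by 0.161/0.125 - 1 = 29%.

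| Slope per 1% | Converted RR (true 1.125) | Inflation of the excess |
|---|---|---|
| 0 | 1.125 | none |
| -0.3 | 1.130 to 1.133 | 4% to 6% |
| -0.5 | 1.138 to 1.146 | 10% to 17% |
| -0.8 | 1.152 to 1.173 | 22% to 38% |
| -1.2 | 1.176 to 1.217 | 41% to 74% |

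**Step 3: the alternatives on the same data.** In the 12 simulated trials the conversion exceeded the crude RR every time (+0.008 to +0.124). Standardising the same logistic fit over the covariate differed from crude by -0.021 to +0.022, and Poisson GEE by -0.041 to +0.001. Averages over the 12: crude 13.826/12 = 1.152, standardised 13.819/12 = 1.152, Poisson 13.601/12 = 1.133, conversion 14.346/12 = 1.196. With single data sets, the crude average need not equal 1.125. A separate set of 40 runs per setting (baseline-to-1-year latent correlation 0.5, 0.6, 0.7) gave conversion 1.150, 1.153, 1.184 and Poisson 1.127, 1.119, 1.124.

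Neither alternative inflates the RR. Poisson GEE sat slightly low in the 12 trials, which used an exchangeable working correlation. The result that a misspecified covariate form leaves the randomised RR on target belongs to the independence working correlation.

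**The case against.** A reader might infer three stronger claims, and the documents support none of them.

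- **That the primary model will fail.** The article gives neither the baseline HbA1c distribution nor its association with the 1-year value. At weaker slopes the model mostly converges, and the plan already foresees failure.
- **That the plan overstates the effect.** It names no conversion formula. Marginal standardisation is also an indirect derivation and lacks this bias. A fuller internal plan, signed off separately according to the article's Results section, may settle the route.
- **That a failed fit would be published in distorted form.** A constrained maximum-likelihood fit on the boundary can shrink the RR, but the plan specifies no such fit; non-convergence leads to the fallback.

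It is also fair that Poisson GEE is still run in the fallback, so the direct RR is ranked lower but not lost. An OR of 1 converts to an RR of 1, so the conversion creates no effect under the null. The composite has no baseline covariate, so the problem does not arise there. Raw percentages by arm are tabulated, so the crude absolute difference can be read off. Sizing the trial "to detect a ≥5% absolute increase in the primary outcome for the intervention group" and reporting an RR is no contradiction.

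What remains is the ranking, which the article fixes in two places, and an RR whose derivation it leaves open.

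**Conclusion.** The point holds in conditional form and should be fixed; it is not critical. No stated figure is wrong. If baseline HbA1c is strongly prognostic (assumed logit slope of about -0.8 per 1% or steeper), the log-binomial GEE may well fail. The tabulated primary RR would then depend on an unstated derivation, with the direct estimator in second place. If that derivation were the simple conversion with the marginal control risk, a true RR of 1.125 would read about 1.14 to 1.22 over slopes of -0.5 to -1.2. These sizes rest on the assumed baseline distribution and slopes and on that formula. They were worked out for HbA1c only; FBG, BP and LDL-C share the model form but were not simulated.

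**What to change.** 1. Make Poisson GEE (log link, robust community-level variance) the first fallback, or the primary model. State the working correlation; independence is the safer choice if the covariate form may be wrong.
2. If logistic GEE is kept, obtain the RR by marginal standardisation, with a cluster-robust or bootstrap CI, and rule out conversion of the OR.
3. Define what counts as non-convergence.
4. Align Table 2, footnote a. In Imputed Data Analyses, say what is pooled when the fallback applies, since the logistic coefficient is a log OR and not a log RR.
5. Apply the same rule to the covariate-adjusted FBG, BP and LDL-C outcomes. The composite needs no change.

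The cost is a few lines of text and a changed distribution or a standardisation step in the program. The downside of Poisson is that some fitted values exceed 1 (0.2% to 7.4% of patients in the nine scenarios where the log-binomial failed). This leaves the RR essentially unaffected, apart from the slight shortfall seen with the exchangeable correlation.
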